**Fig. 4 Fig4:**
[figure not shown]
Schematic overview of a full registration framework for the correlation of the ultrasound image with histopathology. Legend: A 3D reconstruction of the ex-vivo radical prostatectomy specimen and in-vivo gland (Step 1A and 1B); registration between the in-vivo and ex-vivo model (Step 2); Correlation of the pathology data and ultrasound image (Step 3); Pixel-wise superposition of the histopathological data onto the ultrasound image

### Statistical analysis and sample size

Demographic and disease specific characteristics of the study population will be descriptively reported. For localization of PCa, a logistic generalized estimating equation (GEE) model, accounting for the fact that 12 ROIs will be analysed in the same patient, will be used to estimate the sensitivity, specificity, PPV and NPV for the three different US modalities and any combination of those, both for different Likert scale thresholds (Likert ≥3 and Likert ≥4) as for the predefined criteria of clinically significant PCa. In principle, the model will contain US modality, reader and their interaction. Sensitivity is defined as the probability of correctly identifying a tumour focus in a given ROI. Specificity is defined as the probability of correctly identifying ROIs negative for tumour. The effect of histopathological variables (Gleason score, lesion size and pT-stage) will be tested for the sensitivity of each US modality. For detection, readers with Likert scores ≥4 for any clinically significant PCa-containing ROI are considered to have detected PCa in that particular patient. The interobserver agreement will be evaluated using the intraclass correlation coefficient.

No formal sample size calculation was performed. In line with the IDEAL recommendations for explorative studies and published (mpMRI) studies with a similar design a total of 50 patients will be included in the study [35–37].

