## Methods/design

### Study objectives

#### Primary objectives

To determine the diagnostic performance i.e. sensitivity, specificity, PPV and negative predictive value (NPV) of GS, SWE, CEUS with quantitative mapping and their combination, mpUS, for the localization of clinically significant PCa foci.

Clinically significant PCa for the purpose of the primary objectives will be defined as the presence of a histopathologically confirmed Gleason ≥3 + 4 = 7 tumour focus with a tumour volume > 0.5 cm^3^.

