#### Secondary objective(s)

To determine the diagnostic performance i.e. sensitivity, specificity, PPV and NPV of GS, SWE, CEUS with quantitative mapping and their combination mpUS for the detection and localization of PCa foci:for different thresholds of clinical significance; namely presence of a Gleason ≥4 + 3 = 7 tumour focus and presence of a Gleason ≥3 + 4 = 7 tumour focus, independent of volume, respectivelyin relation to the specific region of the prostate (peripheral zone versus transition zone)

To assess the technical feasibility, image quality and procedure related adverse events

To assess the interobserver agreement between US readers with difference levels of experience

To develop a classifier algorithm combining complementary information in the different ultrasound modalities into one single multiparametric map.

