### Histopathologic correlation of imaging

All US imaging, each sequence separate and combined, will be evaluated by US readers in blinded fashion. The four quadrants (left and right peripheral zone and left and right transition zone, respectively) of each imaging plane (base, mid and apex) will be evaluated for the likelihood of clinically significant PCa based on a five-point Likert Scale (1: highly unlikely; 2: unlikely; 3: equivocal; 4: likely; and 5: highly likely), resulting in a total of 12 regions of interest (ROIs) per prostate. Examiners are blinded for clinical and pathological data but aware that patients are scheduled for radical prostatectomy.

Matching of US imaging with histopathology is a challenge; not only do the deformations of the prostate after resection have to be taken into account, but also the mismatch in orientation between imaging planes and pathology slices and deformation due to transrectal probe usage. To provide for an accurate histopathologic correlation a three-step process combing reconstruction, registration and correlation is used in line with our previous published work [25, 26, 34]. First, a 3D histopathological reconstruction with adequate interpolation of tumour delineations into tumour volumes is performed based on the pathology slices. Hereafter, a 3D US model of the in-vivo prostate is reconstructed from the 2D greyscale sweeps [25, 26]. Thirdly, a 3D, surface-based elastic registration method is used to fuse the in-vivo 3D US model with the 3D histopathological model. This method avoids the need of landmarks or a high level of detail, often lacking in greyscale US, while no manual intervention is required during the registration [26]. Lastly, the registered 3D models are correlated to the actual images with superposition of histopathology onto the ultrasound imaging with its 12 ROIs per prostate. Figure 4 provides a schematic overview of a full registration procedure.

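### Sensitivity and specificity are worded against any tumour although the target is clinically significant cancer, so the class of ROIs holding only insignificant tumour is unsettled

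*Protocol article*

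**What the plan says.** The Primary objectives section asks for sensitivity, specificity, PPV and NPV "for the localization of clinically significant PCa foci". It defines significance as "presence of a histopathologically confirmed Gleason ≥3 + 4 = 7 tumour focus with a tumour volume > 0.5 cm"³. The abstract's methods paragraph also names significant cancer as what the primary outcome measures. The Secondary objective(s) section repeats the four measures at two other thresholds: Gleason 4+3 or higher, and Gleason 3+4 or higher whatever the volume. Any cancer at all is not among the listed thresholds.

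The readers' task has the same target. Under Histopathologic correlation of imaging, the quadrants "will be evaluated for the likelihood of clinically significant PCa based on a five-point Likert Scale". Four quadrants are scored in each of three planes, "resulting in a total of 12 regions of interest (ROIs) per prostate".

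The Statistical analysis and sample size section first says that a logistic GEE model will estimate the four measures for the Likert cut-offs of 3 and 4 and for the significance criteria set in advance. It then defines two of them:

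- For the positives: "Sensitivity is defined as the probability of correctly identifying a tumour focus in a given ROI"
- For the negatives: "Specificity is defined as the probability of correctly identifying ROIs negative for tumour"

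Neither sentence mentions significance. PPV and NPV get no separate definition.

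**The concern.** Three kinds of ROI can occur: those with significant cancer, those with only insignificant tumour, and those free of tumour. Under the primary definition the middle kind holds only Gleason 3+3, or a focus of Gleason 3+4 or higher that is no larger than 0.5 cm³. Pathology examines the whole specimen and outlines each focus, so these ROIs will be identified and need a class.

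Against significant cancer they are negatives. Under the literal wording they are not negative for tumour, so they cannot enter the specificity denominator. They either count as positives, if the sensitivity sentence is also taken literally, or drop out of both measures, if sensitivity is kept to significant foci. The tumour-free class would also be identical under all three significance definitions, so specificity could not respond to the threshold being studied.

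The choice affects the primary measures. The Discussion asks whether mpUS could serve as a triage test to exclude significant cancer, as a means of targeting suspicious regions, or both. NPV and PPV bear directly on that question, and both depend on how these ROIs are coded.

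**Working it through.** The plan states no accuracy, prevalence or power figure to reproduce. The only arithmetic it fixes is 50 patients × 12 ROIs = 600 ROIs per reader and modality.

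**Assumed inputs** (none is in the document):

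| ROI class | Number | Read positive | Positive reads | Negative reads |
|---|---|---|---|---|
| Significant cancer | 150 | 70% | 105 | 45 |
| Insignificant tumour only | 90 | 40% | 36 | 54 |
| Tumour-free | 360 | 15% | 54 | 306 |

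**Reading A: insignificant-only ROIs are negatives (target is significant cancer)**
- Sensitivity = 105/150 = 70.0%
- Specificity = (54 + 306)/450 = 80.0%
- PPV = 105/(105 + 36 + 54) = 105/195 = 53.8%
- NPV = 360/(45 + 360) = 360/405 = 88.9%

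**Reading B: insignificant-only ROIs are excluded**
- Sensitivity = 105/150 = 70.0%
- Specificity = 306/360 = 85.0%
- PPV = 105/(105 + 54) = 105/159 = 66.0%
- NPV = 306/(45 + 306) = 306/351 = 87.2%

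**Reading C: insignificant-only ROIs count as tumour-positive**
- Sensitivity = (105 + 36)/(150 + 90) = 141/240 = 58.8%
- Specificity = 306/360 = 85.0%
- PPV = 141/195 = 72.3%
- NPV = 306/405 = 75.6%

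**Direction in general.** Let n_i and n_b be the numbers of insignificant-only and tumour-free ROIs, and q_i and q_b their positive-read rates.

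- Specificity under B or C minus A = n_i(q_i − q_b)/(n_i + n_b). Here that is 90 × (0.40 − 0.15)/450 = 0.05, or 5 points. It is zero when q_i = q_b and negative when q_i < q_b.
- PPV is higher than under A whenever any insignificant-only ROI is read positive. Reading B takes those reads out of the denominator; C adds them to the numerator.
- NPV is lower than under A whenever any such ROI is read negative. The fall is small under B and larger under C.
- Sensitivity is unchanged under B. Under C it falls if these ROIs are read positive less often than significant ones, as would normally be expected.

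**Range under a second set of assumptions.** Take 20% of ROIs as significant, read positive at 70%, and tumour-free ROIs read positive at 20%. Vary the insignificant-only share from 5% to 25% and its positive-read rate from 15% to 50%. C minus A then runs as follows:
- Specificity: from −1.6 to +9.4 points. For the upper end, 0.25 × (0.50 − 0.20)/0.80 = 0.094.
- PPV: from +2.5 points (47.1% to 49.6%) to +33.4 points (37.3% to 70.7%).
- Sensitivity: a fall of 4.0 points (70.0% to 66.0%) to 30.6 points (70.0% to 39.4%).
- NPV: a fall in every case.

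**The case against.** The strongest reply is that tumour is shorthand. The GEE sentence, which comes shortly before the two definitions, ties the same four measures to the predefined significance criteria, and the abstract and primary objective agree with it. The article drops the qualifier elsewhere too: the detection rule requires a high score in an ROI containing significant cancer and then calls the result simply detection of cancer. On this reading ROIs are reclassified for each criterion and nothing is wrong beyond loose wording. The study is also explorative, and ROI coding could be spelled out in a fuller protocol or SAP.

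Much of this stands. The intended reading is available and may well be the right one, so the text does not show that any tumour was chosen as the reference standard. What remains is that these are definitions the article itself states, not details it leaves out. The detection rule in the same paragraph carries the qualifier on the ROI, while the two definitions do not. The analyses with and without ROIs holding small tumours, foreseen in the Discussion, address registration error and do not settle the class.

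A reader might infer that specificity and PPV will be overstated. The document does not support that as a fact. It depends on the literal reading being followed, and for specificity also on insignificant-only ROIs being read positive more often than benign ones, for which no rates are given. It is also one-sided: counting these ROIs as tumour makes NPV, and normally sensitivity, look worse.

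**Conclusion.** The point holds as a conflict of wording in the definitions of the primary measures. The two definition sentences do not match the stated target, the readers' task or the GEE sentence, and the class of ROIs holding only insignificant tumour is left open.

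Under the illustrative inputs the choice moves specificity by 5 points, PPV by 12 to 19 points (53.8% against 66.0% or 72.3%) and NPV by 2 to 13 points (88.9% against 87.2% or 75.6%). Sensitivity falls by 11 points if these ROIs count as tumour. These sizes rest wholly on assumed class counts and read rates. Given the literal wording, the rise in PPV needs only that some such ROI is read positive; the direction for specificity is conditional.

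This should be corrected before the readings are analysed, so that the coding is not chosen after the results are seen. It is not a design failure, because the text allows the intended reading.

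**What to change.** Replace the two definition sentences. For each significance definition and Likert cut-off:

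- Sensitivity is the probability of a score at or above the cut-off in ROIs containing a focus that meets that definition.
- Specificity is the probability of a score below the cut-off in all other ROIs, including those with only insignificant tumour.
- PPV and NPV use the same two classes.

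Report specificity in tumour-free ROIs as a labelled supplementary figure. That keeps the information in the literal wording without letting it stand for the primary measure.

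The cost is two rewritten sentences. No new data are needed, since pathology already grades and outlines each focus. If the literal coding had been intended, PPV would come out lower and NPV higher than under that coding. Specificity would be lower if insignificant-only ROIs are read positive more often than benign ones.

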### Quality and patient safety

Quality of data and patient safety will be continuously monitored by the investigators. Periodical reporting of study progression and patient safety will be performed to the reviewing Institutional Review Board (IRB). The investigator will inform the subjects and the reviewing IRB if anything occurs of which the disadvantages of participation may be significantly greater than was foreseen in the research proposal. The investigators will notify the IRB without undue delay of a temporary halt including reason for such an action. The investigators will take care that all subjects are kept informed.

### Risks and benefits

TRUS imaging of the prostate is safe and well tolerated. There is a small anticipated risk in this study because of the UCA usage. After its use in thousands of patients, adverse events related to UCAs appear to be mild, rare and transient [38–40]. Sensations of warmth, facial or general flushes and itching (at injection site) are the most frequently reported minor side effects. Serious adverse reactions, which consists of hypersensitivity allergic reactions are rare (< 0.01%), but comprehensive rescue measures are prepared and available for all the patients in the study. There is no direct benefit for patients included in this study. Results of this study, however, can be important for future patients in the diagnostic work-up for PCa. Patients will be informed of the risks and absence of benefit, and both will be described in the study information

## Discussion

New ultrasound modalities with quantitative techniques, such as SWE and CEUS with parametric mapping, are gaining interest. The exploration of these techniques in a multiparametric fashion is essential for the development of an ultrasound-based imaging approach with the potential of real-time PCa imaging and targeted biopsy. This study, including a ground truth reference standard, will give insight into different US features of PCa and into its combined diagnostic value. Furthermore this study will provide information on the question whether mpUS could potentially be used as a triage test to exclude significant PCa or should be used to target specific regions suspicious for significant PCa or both. With accurate registration and fusion gaining attention for reliable image-targeted biopsies and (focal) treatment, we believe that our study also contributes to the introduction of suitable registration/fusion options.

Its design with radical prostatectomy specimens as reference standard, however also comes with some disadvantages. First, the population is different from the primary diagnostic setting since men must have PCa and choose to have surgery (spectrum bias). Second, the reader examining the images is aware that there must be PCa, potentially biasing readers towards higher sensitivity readings (observer bias). However, studies using a more appropriate population with prostate biopsy specimens as reference standard, fail to detect all clinically significant lesions found after radical prostatectomy, even in a template-guided transperineal saturation setting [1, 41]. Despite this important limitation of prostate biopsy as reference standard, a biopsy study can be foreseen as next step in the clinical assessment of mpUS imaging for PCa diagnosis. After all, the clinical utility of a targeted biopsy approach for mpUS suspicious lesions cannot be accurately assessed in this study as a targeted biopsy procedure is not only dependent on the scoring of lesions on mpUS but also dependent on other factors such as targeting accuracy, biopsy operator experience and patient movement.

Another limitation of this study is that the prostate is evaluated in 2D US imaging planes. There is a risk of missing tumours outside the predefined imaging planes while the UCA transport kinetics have to be modelled with strong assumptions in its directionality [31]. Although a 3D approach can overcome these limitations and reduce the number of UCA bolus injections, no clinical US device is currently available with both 3D SWE and 3D CEUS imaging.

We have chosen for a stringent 12 region based template per prostate for our analysis. Although, in comparison with the prostate imaging reporting and data system version 2 (PI-RADSv2), this is a limited number of regions, we assume that this approach is the best approximation for US and pathology matching as more ROIs per template would increase the risk of registration errors. Besides the well-known errors in the registration procedure of ultrasound imaging and pathology caused by gland deformation, fixation-related shrinkage and a mismatch in US imaging and pathology orientation, the intraoperative frozen section examination have to be taken into account in our study [42, 43]. To assess the influence of the registration between imaging and histopathology on the final results, separate analyses including and excluding ROIs with small tumors (with respect to the ROIs) and inconsistencies across multiple ROIs are foreseen. Besides, studies with PI-RADSv2 or more ROIs per template often also simplify their template for analysis or use more tolerant approaches for misalignment with inclusion of neighboring regions [44–46].

Lastly, further research regarding improvements to the standardization and reproducibility of these ultrasound modalities as stand-alone tools and in a multiparametric fashion is still required. Various ultrasound manufacturers have introduced SWE into their ultrasound scanners and computer-aided quantification and parametric mapping of CEUS recording with CUDI is not limited to a specific ultrasound scanner. Therefore, there is an increasing need to define quality criteria for these new techniques, provided that results of our study are positive, in order to improve clinical application and generalizability of these techniques in other centres with their own local expertise and resources [47, 48].

Despite these limitations, we expect that the results of this study will contribute to the assessment of the role of mpUS imaging for the diagnosis of PCa in clinical practice. In light of current limitations of prostate biopsy and mpMRI, mpUS holds the potential for an accessible imaging-based PCa approach.

## Abbreviations

(PI-RADSv2): Prostate imaging reporting and data system version 2
AUC: Area under the curve
CEUS: Contrast - enhanced ultrasound
CUDI: Contrast ultrasound dispersion imaging
DRE: Digital rectal examination
EAU: European Association of Urology
GS: Gleason score
IRB: Institutional Review Board
mpMRI: Multiparametric magnetic resonance imaging
mpUS: Multiparametric ultrasound
NPV: Negative predictive value
PCa: Prostate cancer
PPV: Positive predictive value
PSA: Prostate specific antigen
SWE: Shear wave elastography
TIC: Time-intensity-curve
TRUS: Transrectal ultrasound
UCA: Ultrasound contrast agent
